### Secondary outcome assessment

Additionally, inflammatory cells (neutrophils, B- and T-lymphocytes), MMPs and proinflammatory cytokines will be assessed by immunohistochemistry and ELISA as previously described [40, 41]. Circulating concentrations of other AAA biomarkers, including osteoprotegerin, resistin, D-dimer and fasting lipids, will be assessed by ELISA and automated assays as previously described [31, 36–38]. Whole genome microarrays and real-time polymerase chain reaction will be used to examine gene expression levels based on findings from ongoing expression arrays and biomarker studies.

### Study population and power calculation

Estimated outcomes for the control group are based on assessments performed in human AAA biopsies or blood samples from previous studies [28, 32, 42–44]. Estimated effect sizes for fenofibrate therapy are based on previous rodent and human studies, and the consideration of outcomes likely to be required for clinical efficacy [19, 28, 32, 42–44]. To significantly influence the natural history of aortic destruction, it is estimated that a reduction in all primary outcomes assessed within AAA biopsies of at least 50% is likely to be required. In a rodent model, 4 weeks’ treatment with fenofibrate reduced aortic OPN concentration and macrophage infiltration by a median of 95% and 70%, respectively, suggesting that this treatment effect size is realistic [19]. For serum OPN, it has previously been reported that a fibrate reduced circulating OPN concentration by approximately 40% after 4 weeks of treatment [32]. Based on these data, the estimated mean values for control and treatment groups were calculated and are given in Table 2. Sample sizes were calculated using GPower3.1, based on a *t* test as the statistical analysis test. Since there are three primary outcomes, alpha was set at .017, adjusted from .05 for multiple testing. Sample size was estimated based on a power of 80% and equal numbers of participants in each treatment arm. As a result, 20 participants receiving fenofibrate and 20 participants receiving placebo are required. Assuming a dropout rate of 5%, a total of 42 participants will be required.

**Table 2 Tab2:** Summary of primary outcome measures and expected results

Primary outcome	Measurement method	Estimated outcomes	
		Placebo	Fenofibrate
AAA-wall OPN concentration (pg/mg)	ELISA	210 ± 145	84 ± 87
AAA-wall macrophages (per mm^2^ section)	IHC	4.9 ± 1.8	2.4 ± 1.8
Serum OPN concentration (ng/mL)	ELISA	77 ± 32	46 ± 32

*AAA* abdominal aortic aneurysm, *ELISA* enzyme-linked immunosorbent assay, *IHC* immunohistochemistry, *OPN* osteopontin

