Collectively, the above findings lead to the hypothesis that a short course of fenofibrate will exert beneficial effects on AAA by mechanisms involving both serum lipid modification and favourable changes to the AAA wall. The aim of the current study is to assess the effect of fenofibrate taken daily for a minimum of 2 weeks in participants scheduled for elective open AAA repair. This group of patients is particularly suitable since the AAA will be replaced with a prosthetic graft enabling the AAA wall and thrombus to be removed for biological assessment. The primary aim of the study is to determine whether fenofibrate will reduce the relative number of AAA-wall macrophages, reduce the relative concentration of AAA-wall OPN and also reduce the serum concentrations of OPN. The effect of fenofibrate on secondary parameters, including inflammatory cell (neutrophils, B-and T-lymphocytes) number, MMPs and proinflammatory cytokines within the AAA wall, periaortic fat and intramural thrombus, and circulating concentrations of AAA biomarkers, including osteoprotegerin, resistin, D-dimer and fasting lipids, will also be assessed [31, 36–38].

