### Data management and analysis

Trial documentation including protocols, SOPs and CRFs will be shared electronically with participating study centres. Protocol amendments will be submitted to the Royal Brisbane and Women’s Hospital HREC and local site research governance offices and disseminated to the relevant parties at each study site. Data recorded on printed CRFs will be scanned to the study centre in Townsville where it will be entered centrally and examined for data quality. This will allow confirmation of entry criteria and collection of set entry and outcome data. Examples of important baseline data which will be collected include age, gender, presence of diabetes and/or dyslipidaemia, concurrent medications and maximum aortic diameter. At completion of the trial the database will be checked for errors and data confirmed with source documentation where required. Analysis of primary and secondary endpoints will be based on intention-to-treat at the time of randomisation. All participants who meet the eligibility criteria, provide written informed consent and are enrolled in the study will be included in the primary analysis, regardless of adherence to medication allocation.

To identify potential confounders, collected clinical and demographic data will be compared between groups via univariate statistics. The distribution of all continuous data variables will be assessed for normality using the Kolgorov-Smirnov test. Normally distributed continuous variables will be compared between test groups via *t* test; non-normally continuous distributed variables will be compared between groups using the Mann-Whitney *U* test. Nominal data will be compared using the chi-squared test. Characteristics showing a *p* value < 0.100 on univariate tests will be considered as potential confounders and will be entered as covariates in subsequent binary logistic regression models assessing the association of each of the outcome measures with treatment allocation. Following binary logistic regression, the association of all covariates with treatment allocation will be reported as odds ratios and 95% confidence intervals. For all analyses, *p* values <0.05 will be considered to be significant. Data will be published in a peer-reviewed journal with copies of the paper available to participants if required.

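### The three-way alpha split at .017 used for sample size is not carried into the analysis, which uses p < 0.05; a Holm step-down would reconcile the two and raise per-outcome power at no extra patients

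*Protocol article*

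**What the plan says.** All references are to the protocol article; no separate statistical analysis plan is shown.

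Under Study population and power calculation:
- Multiplicity: "Since there are three primary outcomes, alpha was set at .017, adjusted from .05 for multiple testing".
- Test: "Sample sizes were calculated using GPower3.1, based on a *t* test as the statistical analysis test". One- or two-sided is not stated.
- Power: "Sample size was estimated based on a power of 80% and equal numbers of participants in each treatment arm". The section does not say whether the 80% is per outcome or joint.
- Result: "As a result, 20 participants receiving fenofibrate and 20 participants receiving placebo are required", and then "Assuming a dropout rate of 5%, a total of 42 participants will be required".
- Table 2 gives the expected values, placebo against fenofibrate: wall OPN 210 ± 145 and 84 ± 87 pg/mg; wall macrophages 4.9 ± 1.8 and 2.4 ± 1.8 per mm²; serum OPN 77 ± 32 and 46 ± 32 ng/mL.

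Under Data management and analysis: "For all analyses, *p* values <0.05 will be considered to be significant". The .017 level does not appear there, and no exception is made for the primary outcomes.

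**The concern.** Two thresholds are given for the same three tests. Dividing 0.05 by three at the design stage protects against a false claim on any one of three primaries. That protection exists only if the analysis uses the same rule. If each primary is judged at 0.05, the chance of at least one false positive when fenofibrate does nothing is well above 5%. A result with p between .017 and .05 on one outcome would be positive under one section and negative under the other.

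Simply changing 0.05 to .017 would settle the conflict, but at a cost. A flat split keeps .017 for the second and third outcomes even after the first has been rejected. In a 40-patient trial whose authors expect all three effects, that gives away power which a step-down test recovers at the same error rate.

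**Working it through.** **Inputs.** Means and SDs from Table 2; alpha .017; 20 per arm. Not in the document, so assumed: sidedness (both tried) and the within-patient correlation between the three outcomes (a common value, 0 to 0.8).

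**Step 1, standardised effects.** d = difference / √((s₁² + s₂²)/2).
- Wall OPN: 126 / √((145² + 87²)/2) = 126 / 119.6 = 1.054
- Macrophages: 2.5 / 1.8 = 1.389
- Serum OPN: 31 / 32 = 0.969

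**Step 2, reproduce the plan's figure.** Two-sample t test, noncentral t, noncentrality d·√(n/2), 2n − 2 degrees of freedom, 80% power.

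| Patients needed per arm | Wall OPN | Macrophages | Serum OPN | Largest |
|---|---|---|---|---|
| One-sided .017 | 17 | 11 | 20 | 20 |
| Two-sided .017 | 21 | 13 | 24 | 24 |

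The planned 20 per arm matches one-sided .017 exactly and does not match two-sided .017. The total of 42 is 40 × 1.05.

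**Step 3, power per outcome at 20 per arm with the flat .017.** The noncentralities are 3.33, 4.39 and 3.06 on 38 degrees of freedom.

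| | Wall OPN | Macrophages | Serum OPN |
|---|---|---|---|
| Two-sided | 79.4% | 96.7% | 71.3% |
| One-sided | 86.7% | 98.4% | 80.3% |

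If the tests are two-sided, serum OPN falls clearly short of 80% and wall OPN falls short by less than one point.

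**Step 4, error rate if 0.05 is applied to each primary.** Under the global null with independent outcomes, 1 − 0.95³ = 14.3%. Positive correlation lowers this, but it stays above 5%.

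**Step 5, Holm.** Order the three p values. Compare the smallest with .05/3 = .0167, the next with .05/2 = .025 and the largest with .05, stopping at the first failure. Power at 20 per arm comes from simulation (200,000 trials per setting, normal data, Table 2 means and SDs, correlation 0 to 0.8):

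| Holm | Wall OPN | Macrophages | Serum OPN |
|---|---|---|---|
| Two-sided | 86-88% | 97-98% | 82-83% |
| One-sided (family-wise 0.05, one-sided) | 92-94% | about 99% | about 90% |

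Under the global null, Holm and Bonferroni each reject at least one hypothesis in 5.0% of trials at correlation 0 and about 4.5% at 0.5. The gain is therefore not bought with extra type I error.

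**Step 6, supplementary.** Chance that all three are significant, for correlation 0 to 0.8: two-sided, flat 54-66% and Holm 75-80%; one-sided, flat 68-76% and Holm 86-88%.

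**The case against.** **A stronger reading to avoid.** A reader might infer that all three outcomes must succeed, and so that the trial has only a 54-66% chance of meeting its aim. Two passages invite this. Background gives the aim as to "reduce the relative concentration of AAA-wall OPN and also reduce the serum concentrations of OPN" as well as to lower macrophage number, and the power section says that "a reduction in all primary outcomes assessed within AAA biopsies of at least 50% is likely to be required". Neither sets such a rule. The first lists three things to be determined. The second covers only the two biopsy outcomes, leaves out serum OPN, and serves to justify an assumed effect size. Splitting alpha over three outcomes is the usual design for separate claims. On that reading the chance of at least one success at .017 is 97% or more. If all three really were required, no split would be needed: each tested at .05 gives 75-82% two-sided, slightly above Holm. The 54-66% also assumes two-sided tests.

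**Bonferroni is valid, so Holm is only a preference.** It is true that the flat split controls the error rate. But Holm rejects whatever Bonferroni rejects, sometimes more, under the same guarantee. The analysis section has to be corrected anyway.

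**The power shortfall may not exist.** This stands in part. With one-sided tests the stated 80% is met for every outcome. The document does not say which was meant, so a shortfall is shown only for two-sided tests.

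**A full protocol or analysis plan may settle this.** That is a fair answer to any complaint that a success rule is missing, and none is made here. It does not answer the conflict, because the article positively states 0.05 for all analyses.

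**Conclusion.** The point holds. The document gives .017 in one section and 0.05 in another for the same primary tests, and only the first controls the family-wise error. That contradiction rests on no assumption.

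The efficiency point also holds. At 20 per arm and two-sided, moving from the flat split to Holm gains about 11-12 points for serum OPN (71% to 82-83%) and 7-9 points for wall OPN (79% to 86-88%), with little change for macrophages. One-sided, the gains are about 10 and 5-7 points. These figures rest on t tests, the Table 2 means and SDs, an assumed correlation of 0 to 0.8, and all three effects being real. If only one effect is real, Holm does little better than the flat split for that outcome, but never worse.

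The documents do not show that the trial fails a joint success criterion, because they state none. Nor do they show that it is underpowered regardless of sidedness.

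**What to change.** 1. In Data management and analysis, replace 0.05 for the three primary outcomes with Holm at a family-wise 0.05: smallest p against .0167, next against .025, largest against .05, stopping at the first failure. Say that conclusions are drawn per outcome and that 0.05 applies only to the other analyses.
2. In Study population and power calculation, state whether the tests are one- or two-sided, and use the same choice in the analysis.
3. Restate power as per outcome under the Holm rule, with the assumed correlation range. The chance that all three are significant may be added as supplementary information, labelled as not being the success criterion.

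The cost is a few sentences, settled before unblinding, with no extra patients or data. The one real downside is that confidence intervals matched to Holm are less simple than fixed 98.3% intervals. If simple intervals matter more, carrying .017 into the analysis section would also remove the contradiction, but would leave the power in step 3 of the working unchanged.

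### The 80% power claimed at 20 per arm holds for serum OPN only under an undeclared one-sided test, and wall OPN is sized on a 60% reduction although the text names at least 50% as the target

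*Protocol article*

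**What the plan says.** All inputs are in the protocol article, section 'Study population and power calculation'. The software is named ("Sample sizes were calculated using GPower3.1"), the test is a t test, and for the three primary outcomes "alpha was set at .017, adjusted from .05 for multiple testing". Power and allocation follow: "Sample size was estimated based on a power of 80% and equal numbers of participants in each treatment arm". The result is that "20 participants receiving fenofibrate and 20 participants receiving placebo are required", raised to 42 in total for 5% dropout.

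On the effect to be detected, the same section says that "a reduction in all primary outcomes assessed within AAA biopsies of at least 50% is likely to be required". Table 2 gives the design values (mean ± SD, placebo then fenofibrate): wall OPN 210 ± 145 and 84 ± 87 pg/mg; wall macrophages 4.9 ± 1.8 and 2.4 ± 1.8 per mm²; serum OPN 77 ± 32 and 46 ± 32 ng/mL.

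Neither this section nor 'Data management and analysis' says whether tests are one- or two-sided. The latter lists t tests, Mann-Whitney and chi-squared tests without a direction, plans odds ratios "reported as odds ratios and 95% confidence intervals", and states that p "values <0.05 will be considered to be significant".

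**The concern.** The article prints every input to its calculation except the number of tails, and the answer depends on that choice. A reader who assumes two-sided tests, as is usual when nothing else is said, cannot reproduce 20 per arm and would believe that serum OPN has 80% power when it has about 71%. The chance of missing the assumed serum effect would then be about 29%, not 20%.

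The second issue does not depend on sidedness. If a 50% fall in the biopsy outcomes is the smallest that matters, readers will take the trial as powered to detect it. For macrophages the design value is close to that (51%). For wall OPN it is 60%, with no reason given for the difference.

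In both cases a null OPN result would be read as stronger evidence against fenofibrate than the design supports.

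**Working it through.** **Inputs.** Table 2 means and SDs; alpha .017; 80% power; equal arms; t test.

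**Method.** Two-sample t test by the noncentral t distribution. Effect size d = difference / s, with s = √((s₁² + s₂²)/2). With n per arm, df = 2n − 2 and noncentrality δ = d√(n/2). Power is the probability that t exceeds the critical value (beyond either critical value if two-sided). At n = 20, df = 38, √(20/2) = 3.162, and the critical value at .017 is 2.199 one-sided and 2.496 two-sided.

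**Step 1: effect sizes.**
- Serum OPN: (77 − 46)/32 = 31/32 = 0.969; δ = 3.063. Reduction 31/77 = 40%.
- Wall OPN: s = √((145² + 87²)/2) = 119.6; d = 126/119.6 = 1.054; δ = 3.33. Reduction 126/210 = 60%.
- Macrophages: 2.5/1.8 = 1.389; δ = 4.39. Reduction 2.5/4.9 = 51%.

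**Step 2: reproduce 20 per arm, then test the other reading.**

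| Outcome | One-sided .017: n per arm for 80% | Power at 20 | Two-sided .017: n per arm for 80% | Power at 20 |
|---|---|---|---|---|
| Wall OPN (60%) | 17 | 86.7% | 21 | 79.4% |
| Macrophages | 11 | 98.4% | 13 | 96.7% |
| Serum OPN | 20 | 80.3% | 24 | 71.3% |

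One-sided, the largest requirement is exactly 20, set by serum OPN, so the printed figure is reproduced. Two-sided, the largest is 24 per arm (48 against 40 in total). Using .05/3 in place of .017 leaves serum OPN at 20 per arm one-sided and 24 two-sided. Simulation of the two-sided t test at 20 per arm gave 71.4% for serum OPN and 79.4% for wall OPN.

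**Step 3: wall OPN at exactly 50%.** A 50% reduction is 210 to 105, a difference of 105. The documents give no fenofibrate SD at that mean, so it must be assumed. Power at 20 per arm, alpha .017:

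| Assumed fenofibrate SD | d | Two-sided | One-sided |
|---|---|---|---|
| 72.5 (placebo CV kept: 105 × 145/210) | 0.916 | 65.6% | 75.5% |
| 87 (Table 2 SD kept) | 0.878 | 61.3% | 71.7% |
| 109 (Table 2 fenofibrate CV kept: 105 × 87/84) | 0.819 | 54.3% | 65.3% |
| 145 (same as placebo) | 0.724 | 42.8% | 54.1% |

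No row reaches 80%. With SD 87, 80% power needs 29 per arm two-sided or 24 one-sided.

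**Step 4: can baseline serum help?** Serum is collected at the initial visit and again on the day of surgery. Adjusting for baseline with correlation r divides the SD by √(1 − r²). At r = 0.41 the effective d is 0.969/√(1 − 0.168) = 1.062, and two-sided power at .017 with 20 per arm is 80%. The documents give no value of r. There is no pre-treatment biopsy, so this route is closed for wall OPN.

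**The case against.** The strongest reply is that the printed sample size is not wrong. It is the exact answer for a one-sided test, and the primary aim is directional: fenofibrate is to "reduce the relative concentration of AAA-wall OPN and also reduce the serum concentrations of OPN". A condensed article may also leave sidedness to the full protocol. This stands in part. A reader might infer that planned power is 71%, but no passage fixes two-sided testing. The 95% intervals belong to logistic-regression odds ratios and are a pointer, not a declaration. Equally, a directional aim is a hypothesis and does not declare a one-sided test. What remains is that the printed result depends on an unstated choice, and the usual reading does not give 80%.

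A second reply is that the analysis section tests at .05, where two-sided serum power at 20 per arm is 84.7%. That is true, but it abandons the .017 on which the sample size rests. The conflict between the two thresholds is a separate matter and does not rescue the stated calculation.

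Third, a reader might infer that the 50% sentence and Table 2 contradict each other. They do not: 60% satisfies a floor of at least 50%, and the section cites a median 95% fall in aortic OPN in a rodent model. The two are poorly linked. Nor is it right that wall OPN reaches 80% only at a 60% reduction. One-sided, with Table 2's SDs, about 55% suffices; two-sided, 60% gives 79.4%, a shortfall of one participant per arm. Still, power at the 50% floor is below 80% on either reading.

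**Conclusion.** The point holds in this form. At alpha .017 with 20 per arm, 80% power for serum OPN requires a one-sided test that the article does not declare. Read two-sided, power is about 71% for serum OPN, 79% for wall OPN at Table 2's values (practically the stated 80%) and 97% for macrophages, so the two-sided shortfall of consequence at the design values is serum OPN alone. These figures rest on Table 2's means and SDs and on the t test.

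For wall OPN at the 50% floor, power is about 43–66% two-sided and 54–76% one-sided over fenofibrate SDs from 145 down to 72.5. The single figures of 61% and 72% hold only if SD 87 is kept, which is an assumption. This part of the point stands whichever sidedness was meant.

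**What to change.** 1. State whether the primary tests are one- or two-sided.
2. If two-sided, restate power at 20 per arm and .017 per outcome: about 71% (serum OPN), 79% (wall OPN at a 60% reduction) and 97% (macrophages). If one-sided, say so in both the sample-size and the analysis sections.
3. State that wall OPN is powered for a 60% reduction, and give the lower power at 50% together with the SD assumed.
4. Optionally, adjust serum OPN for its value at the initial visit. This needs no new samples, but it restores 80% two-sided power only if the baseline correlation is about 0.41 or more, which is an assumption. It does nothing for wall OPN, so it should not be offered as general reassurance that the sample size is adequate.

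Items 1 to 3 cost a rewritten power paragraph, plus one sentence in the analysis section if the tests are one-sided. If two-sided, the stated power becomes less favourable. Keeping 80% two-sided by enrolment instead would take 24 per arm for serum OPN: 48 in total, or 48/0.95 = 51 with 5% dropout.

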### Safety

Participant safety will be assessed prior to the administration of the medication and at the end of the study period. At the initial visit, a consultation with a physician will occur, during which the participant will be informed about known side effects including symptoms of abdominal/back pain, chest pain, and renal and liver dysfunction. Pathology tests consisting of full blood count, fasting lipids, glucose, inflammation markers, liver and renal function will be performed. The participant will undergo a physical assessment which will include blood pressure and heart rate measurements that will be reviewed by a physician along with the results of pathology tests prior to randomisation. At the final visit, pathology tests as per the initial visit will be performed and reviewed by a physician. Any adverse event will be reported to the coordinating centre and carefully monitored throughout the study. Serious adverse events (SAEs) will be defined as death, requirement for inpatient hospital treatment and persistent or significant disability. All SAEs will be reported by the site principle investigator to the HREC and reviewed by the chief principle investigator, where a decision regarding withdrawal of trial medication will be made. Where a decision to withdraw trial medication is made, participants will be encouraged to remain on the study protocol. Previous studies suggest that fenofibrate is a relatively safe medication [45, 46]. Participants who are concurrently on warfarin will have two additional safety assessments after randomisation. Current routine care for patients on warfarin involves ongoing measurement of International Normalised Ratio (INR) levels, which in turn dictates the dose of medication required to manage clotting without increasing the risk of excessive bleeding. Participants will be instructed to have their INR concentrations assessed via their usual system at 3–5 days and again at 14–21 days post first dose so that warfarin dosage may be adjusted accordingly.

